### 2.4 Study design

The study was pre-registered within the Open Science Framework (OSF) repository.^1^

### 2.5 Procedure

The study will be conducted *via* the mobile application *Nałogometr*, a proprietary custom-design mobile app available from Google Play or the App Store. The download and onboarding process in the app will be used as baseline data in the study. Upon first use, the app will automatically navigate the participant through necessary permissions and consent about the collection of different types of data. After logging in, participants will be asked to complete a baseline onboarding questionnaire that collects demographic information and their substance use or behavioral habits.

### 2.6 Randomization

Randomization will be applied using an automated balancing algorithm. The algorithm will aim to partition participants into groups based on the initial onboarding assessment to make the resulting groups as balanced as possible concerning the characteristics outlined in the study design section, i.e., (1) primary addiction type; (2) participation in addiction-related therapy; (3) gender; (4) age; (5) addiction severity; (6) abstinence duration. Following randomization, participants in groups 1–12 will receive access to the intervention modules following a 5-day delay. In conditions 1:10, participants get access to the short-term intervention module and one type of long-term intervention. In condition 11, participants get access to the short-term intervention module and all long-term interventions. In condition 12, participants get access only to the short-term intervention module.

Participants in the waitlist control group will be able to access all intervention materials 5 weeks following study enrollment (see Figure 1).

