### 2.8 Measures

Sociodemographic data include gender, age, and place of residence. Substance use-related questions include frequency of use, lifetime use, treatment seeking, and abstinence period (see Supplementary Tables 1, 2). The study includes EMA (three times a day) assessing several variables: craving, lapses, mood, arousal, pressure, anxiety, procrastination, loneliness, tiredness, anger, hunger, and uncertainty (see Supplementary Table 3).

Moreover, the questionnaire assessment will occur three times during the study period (see Table 2).

**TABLE 2 T2:** Timeline of the questionnaire assessment.

Assessment instrument	Baseline (week 1)	Follow-up (week 5)	Follow-up (month 6)
Socio-demographic questions	*x*		
Substances use-related measures			
Psychological dependence (SDS)	*x*	*x*	*x*
Alcohol (AUDIT)	*x*	*x*	*x*
Stimulants (DUDIT)	*x*	*x*	*x*
Psychopathological symptoms measures			
Depression and anxiety (HADS)	*x*	*x*	*x*
Psychological functioning measures			
Sensation seeking (BSSS)	*x*	*x*	*x*
Emotion regulation (DERS)	*x*	*x*	*x*
Impulsivity (UPPS-P)	*x*	*x*	*x*
Coping with stress (Mini-COPE)	*x*	*x*	*x*
Life satisfaction (SWLS)	*x*	*x*	*x*

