### 2.9 Data analysis

We will use factorial design mixed-effects models to compare questionnaire battery scores between experimental groups and the control across measurements. In addition, we will perform an interrupted time series analysis to compare the longitudinal effects of the introduction of different types of interventions on longitudinal EMA outcomes.

We will include participants who complete at least 21 EMA assessments spread across the intervention testing period of 5 weeks. Furthermore, for the 6-month follow-up intervention effects retention analysis, we will include participants who complete at least three EMA assessments within the follow-up period. Moreover, in each intervention group, we will retain participants who log onto the app and use the long-term and short-term self-guided intervention modules at least four times and once, respectively, defined as minimal therapeutic exposure. Finally, for the secondary outcome analysis, we will include participants who complete the baseline and at least one follow-up assessment.

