## 3 Discussion

This study protocol describes a randomized controlled trial designed to determine the effectiveness of self-guided psychological intervention modules delivered *via* a smartphone app (*Nałogometr*). We aim to examine whether and which interventions can effectively reduce craving and lapse risk in problematic alcohol or stimulant use. The embedded trial and analysis will evaluate the effectiveness of intervention modules for alcohol or/and stimulants use. In exploratory analyses, we investigate whether user engagement moderates or changes in psychological functioning measures (e.g., sensation seeking, impulsivity, stress coping, emotion regulation) mediate the effectiveness of the interventions. We hope to determine if these interventions delivered through mobile devices can be effective and contribute to future prevention or therapy addiction programs. The wide availability and accessibility of developed interventions are a substantial advantage. Mobile app interventions may reduce treatment barriers by staying anonymous and avoiding stigma and may be especially useful in places where professional help is unavailable (49–52). We plan a 6 months follow-up to conduct a longer-term evaluation and check the sustainability of the potential change in the user’s behavior–it is an essential factor for relapse prevention through the management of craving. Such a complex study of 13 conditions will allow us to understand better which long-term interventions are most effective. We include multiple intervention types to better assess their effectiveness across diverse individuals. One limitation of the present study could be that the participant dropout will be higher than expected based on previous research (53, 54). Due to the lack of personal contact with researchers and no additional incentives, e.g., prizes or monetary remuneration, the commitment to participate throughout the study may be lower, and motivation may decrease over time.

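### At month 6 the waitlist is no longer an untreated control, so the planned comparison with it on the questionnaire scores measures immediate versus delayed access, not sustained benefit

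*Protocol article*

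**What the plan says.** Section 2.6 (Randomization) sets out thirteen conditions. Arms 1–10 get the short-term module and one type of long-term module, arm 11 gets the short-term module and all long-term modules, and arm 12 gets the short-term module only. These start after a 5-day delay. For the thirteenth condition: "Participants in the waitlist control group will be able to access all intervention materials 5 weeks following study enrollment".

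Section 2.8 (Measures) says that "the questionnaire assessment will occur three times during the study period". Table 2 gives the occasions as week 1, week 5 and month 6, and marks every secondary scale (AUDIT, DUDIT, SDS, HADS, SWLS) at all three.

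Section 2.9 (Data analysis) states: "We will use factorial design mixed-effects models to compare questionnaire battery scores between experimental groups and the control across measurements". It does not restrict this to week 5. Its inclusion rule for the secondary outcomes asks for baseline and at least one follow-up, so a participant whose only follow-up is month 6 would qualify.

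For the EMA data, section 2.9 adds that "for the 6-month follow-up intervention effects retention analysis, we will include participants who complete at least three EMA assessments within the follow-up period". No comparator is named there.

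Section 3 (Discussion) gives the purpose: "We plan a 6 months follow-up to conduct a longer-term evaluation and check the sustainability of the potential change". The limitation it names is dropout and falling motivation. The waitlist's access after week 5 is not mentioned.

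**The concern.** Three statements that are each reasonable do not fit together. The control group is offered the whole package at 5 weeks, the questionnaires are repeated at month 6, and the model compares active groups with that control on every occasion. At month 6 there is no group without access to the intervention.

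All the secondary outcomes are affected, and with them any conclusion about durability that rests on the waitlist. If the former waitlist improves once it has access, a real and lasting benefit in the active arms would show as a shrinking difference and could be reported as an effect that wore off. The objection is not to giving the waitlist access. It is to using the waitlist afterwards, without relabelling, as the control.

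**Working it through.** **The plan's own figure.** The only sample-size figure is 650 participants for 80% power (section 2.3). It can be neither confirmed nor refuted, because the numeric effect size, alpha, the intraclass correlation and the tested contrast are not given. The point does not depend on it. It is used below only for an illustrative arm size.

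**Inputs from the article.** Waitlist access opens at 5 weeks (2.6). Questionnaires are at week 1, week 5 and month 6 (Table 2). There are 13 arms (Abstract) and 650 participants (2.3). The effect is described only as small (2.3).

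**Assumptions.** Month 6 is 26 weeks from enrolment. The true effect against no intervention is d = 0.20 SD. Allocation is equal. The test is two-sided at 0.05. The catch-up fraction f, the share of the effect that the waitlist gains after week 5, is unknown and is varied from 0 to 1.

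**Step 1: length of access.** 26 − 5 = 21 weeks at most before the month-6 questionnaire.

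**Step 2: expected contrast.** Active minus former waitlist = d × (1 − f).

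**Step 3: illustrative power for one month-6 score.** Arm size 650 / 13 = 50. Power counts rejections in the direction of benefit only, so it is 2.5% when the contrast is zero.

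| f | Contrast, 0.20 × (1 − f) | Power, 50 vs 50 | Power, 50 vs 600 (all active arms pooled) |
|---|---|---|---|
| 0 | 0.20 | 17% | 27% |
| 0.25 | 0.15 | 11% | 17% |
| 0.50 | 0.10 | 7% | 10% |
| 0.75 | 0.05 | 4% | 5% |
| 1 | 0 | 2.5% | 2.5% |

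With d = 0.30, power at 50 vs 50 falls from 32% (f = 0) to 11% (f = 0.5).

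**Step 4: could the sign change?** Only if f exceeds 1, meaning that the waitlist gains more from the full package than the active arm has gained from its own modules. Take uptake u and a package effect D among those who use it. The contrast is d − u × D. With d = 0.20 and u = 0.5, D would have to exceed 0.40. This also requires arms 1–10 and 12 to remain limited to their assigned modules up to month 6, which the article does not state.

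**Step 5: what is not affected.**
- The EMA analysis of the primary outcomes uses a 5-week testing period, during which the waitlist has no modules.
- The baseline-to-week-5 questionnaire contrast is sound if the questionnaire is completed before access opens. On ordinary counting, week 5 is days 29–35, which precedes an unlock after five full weeks, but no order is stated.
- Month-6 comparisons among arms 1–12 do not use the waitlist.

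**The case against.** The strongest reply is that randomisation still protects the month-6 comparison. Active versus former waitlist is an unbiased comparison of immediate with delayed access, a mixed model can give separate week-5 and month-6 contrasts, and the exact contrast is normally left to an analysis plan that is not shown. The primary outcomes are hardly touched. The 6-month EMA analysis names no comparator and could mean maintenance within each arm. Access is also not use, so the dilution may be small.

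Most of this stands, and it limits the point to the secondary questionnaire outcomes at month 6. It does not remove the point. Section 2.9 itself names the comparator and attaches it to all measurements, nothing in the article calls the month-6 contrast immediate versus delayed access, and the stated purpose is sustainability. Unknown uptake makes the size unknown, not zero.

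Several stronger readings are tempting but not supported:
- A reader might infer that the waitlist ends up with more than arms 1–10 ever receive. The article gives those arms' initial access and is silent on later access, so this, and any reversal of sign, is conditional.
- A reader might infer that week-5 scores are contaminated. That is possible only if some questionnaires are completed after the unlock.
- A reader might infer that the model pools all three occasions into one group effect. The text does not say so.
- A reader might conclude that the trial's main result is biased. The 5-week analyses do not bear that out.

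**Conclusion.** The point holds for the month-6 comparison of the active arms with the waitlist on the secondary questionnaire scores. As written, the plan calls the comparator a control when it may have had up to about 21 weeks of access to all materials. The contrast estimates immediate versus delayed access. As an estimate of benefit against no intervention it is likely biased toward the null.

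The article gives neither uptake nor a numeric effect, so the size cannot be fixed. Under an assumed 0.20 SD effect, the visible contrast is 0.15, 0.10 or 0.05 SD at a catch-up of 25%, 50% or 75%. The direction is the likely one, not a certainty.

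**What to change.** Amend section 2.9 as follows.

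1. Limit waitlist-controlled inference on the questionnaire scores to baseline versus week 5, from a model with occasion-specific contrasts.
2. Count as week-5 data only questionnaires completed before the waitlist's access opens.
3. At month 6, label any contrast with the former waitlist as immediate versus delayed access. It can stay as a randomised comparison under that name.
4. Base the other month-6 randomised comparisons on arms 1–12, for example with arm 12 as reference. State what the active arms can open after week 5, because the meaning of these comparisons depends on it.
5. State that the trial cannot estimate a 6-month effect against no intervention.

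The cost is a few sentences and a check in the app of questionnaire completion times against the unlock. No participants are added and nobody's access changes. The drawback is a narrower 6-month claim.

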**FIGURE 1 F1:**
[figure not shown]
Participant flow chart.

The study will take place from June 2022 until September 2022, with ongoing participant recruitment. The study includes ecological momentary assessment (EMA), assessing several variables important linked to lapse risk. Participants will be asked three times daily to answer questions about their mood, psychological and physiological state, craving, and if lapses occur. EMA will be administered daily between 6 a.m. and 12 a.m (morning EMA) and between 4 p.m. and 10 p.m. (evening EMA). Participants can select a specific time for assessment delivery that best suits their schedule and needs. When prompted to complete the EMA, participants will have the time to complete it until the next scheduled. Assessments are designed to take less than 2 min to complete. In addition, participants will be able to initiate assessments themselves to not skip any measurements for the day.

### 2.7 Digital therapeutic app *Nałogometr*

#### 2.7.1 Mobile application

*Nałogometr*^2^ is a mobile application dedicated to reducing craving and lapse risk among users with substance use disorder or problematic substance use. The Predictwatch company creates the app. The app includes a dashboard, sobriety calendar, EMA modules, and self-guided psychological interventions. A team of scientists and addiction treatment specialists created the content.

##### 2.7.1.1 Dashboard

The mobile app dashboard is simple and easy to use, allowing quick access to EMA, sobriety calendar, and information about sober and not-sober days. Access to self-guided psychological interventions and weekly feedback is also available.

##### 2.7.1.2 Weekly feedback reports

The mobile app automatically processes and analyzes EMA data entered by the user and generates personalized feedback for the past 7 days. Reports contain information about sober and non-sober days, changes in craving and lapse risk relative to the previous week, and finally, the relationships between craving and the three most important EMA items and protective factors.

##### 2.7.1.3 Self-guided psychological intervention modules

Two main self-guided intervention modules were created for a mobile app: (1) short-term self-guided intervention module and (2) long-term self-guided intervention module (Table 1 and Figure 2). The delivery of these interventions will be initiated 5 days following study enrollment.

**TABLE 1 T1:** Intervention modules in the mobile app.

Intervention modules	Description
Short-term interventions	This module consists of audio-guided sessions on gratitude, auto-empathy, thoughts management, and relaxation. Moreover, they are based on breath relaxation exercises, craving management, and motivation to change.
**Long-term interventions**	
Meditations	Audio-guided meditation sessions focused on increasing the awareness of emotions, effectively reading body signals, and coping with stress.
Mindfulness	Audio-guided sessions on mindfulness of the breath, body, thoughts, and emotions.
My beliefs	Thought management technique based on CBT
Thinking traps	Thought management technique based on CBT (reframing thoughts)
Journey to sobriety	Audio-guided sessions
Planner	Improves goal achievement and self-efficacy.
Mood journal	Improves understanding of the relationship between situations, thoughts, mood and sobriety.
Dream diary	Improves self-observation and awareness of emotions.
Success diary	Enhances self-confidence and self-esteem.
Gratitude journal	Enhances positive attitude.

**FIGURE 2 F2:**
[figure not shown]
Example screenshots of the self-guided intervention modules in *Nałogometr*.

### 2.8 Measures

Sociodemographic data include gender, age, and place of residence. Substance use-related questions include frequency of use, lifetime use, treatment seeking, and abstinence period (see Supplementary Tables 1, 2). The study includes EMA (three times a day) assessing several variables: craving, lapses, mood, arousal, pressure, anxiety, procrastination, loneliness, tiredness, anger, hunger, and uncertainty (see Supplementary Table 3).

Moreover, the questionnaire assessment will occur three times during the study period (see Table 2).

**TABLE 2 T2:** Timeline of the questionnaire assessment.

Assessment instrument	Baseline (week 1)	Follow-up (week 5)	Follow-up (month 6)
Socio-demographic questions	*x*		
Substances use-related measures			
Psychological dependence (SDS)	*x*	*x*	*x*
Alcohol (AUDIT)	*x*	*x*	*x*
Stimulants (DUDIT)	*x*	*x*	*x*
Psychopathological symptoms measures			
Depression and anxiety (HADS)	*x*	*x*	*x*
Psychological functioning measures			
Sensation seeking (BSSS)	*x*	*x*	*x*
Emotion regulation (DERS)	*x*	*x*	*x*
Impulsivity (UPPS-P)	*x*	*x*	*x*
Coping with stress (Mini-COPE)	*x*	*x*	*x*
Life satisfaction (SWLS)	*x*	*x*	*x*

#### 2.8.1 Primary outcome

The primary outcomes of interest are the self-reported lapses (number of lapses reported in daily EMA) and addiction craving (intensity of the urge to use a given substance at the moment of completing the assessment) (see Supplementary Table 3).

#### 2.8.2 Secondary outcomes

Problematic alcohol use is measured with an Alcohol Use Disorders Identification Test (AUDIT) (39), a 10-item one-dimensional tool. Participants answer the questions in terms of standard drinks units. AUDIT assesses the amount and frequency of alcohol intake (items 1–3), alcohol dependence (questions 4–6), and problems related to alcohol consumption (items 7–10). Questions 1 to 8 are scored on a 5-point scale ranging from 0 to 4, and questions 9 and 10 are scored as 0, 2, or 4. Total scores range from 0 to 40; the cut-off point to identify hazardous alcohol intake is 8. A score between 16 and 19 indicates harmful alcohol use, and scores above 20 points indicate possible alcohol use disorder.

The Severity of Dependence Scale (SDS) (40) provides a self-reported measure of the psychological aspects of stimulants and alcohol dependence. A five-item, one-dimensional tool has a uniform scale for questions 1–4 from 0 (“never or almost never”) to 3 (“always”). Question 5 has the same scale with different signatures where 0 means “not difficult at all” and 3 means “impossible.” A score ranging from 0 to 15, where the cut-off score depends on the user’s drug type—a cut-off of ≤ 3 has been used for indexing alcohol dependence (41) and ≤ 5 for indexing amphetamine dependence (42).

The Drug Use Disorders Identification Test (DUDIT) measures self-reported problematic drug use (43). The DUDIT is an 11-item screening instrument, the first nine items are scored on a 5-point scale ranging from 0 to 4, and the last two are scored on a 3-point scale with values 0, 2, and 4. The overall score is calculated by summing the scores on all items, with a maximum score of 44. Previous research in adults established a score of > 24 for both sexes as a cut-off score for dependence (43).

Depression and anxiety are assessed with Hospital Anxiety and Depression Scale (HADS) (44), a 14 items two-dimensional tool. Each subscale consists of 7 items, scoring from 0 to 3. For each subscale, scores between 8 and 10 indicate mild depression/anxiety, and scores between 11 and 21 indicate depression/anxiety disorder.

Participants’ satisfaction with their life is assessed with The Satisfaction With Life Scale (SWLS) (45). SWLS is a short self-report instrument on which participants agree to five statements about life satisfaction on a seven-point Likert scale. A maximum score is 35, and higher scores indicate a high level of life satisfaction.

#### 2.8.3 Additional variables

The sensation-seeking trait is assessed with the Brief Sensation Seeking Scale (BSSS) (46)—an 8-items four-dimensional tool: (1) Disinhibition, (2) Boredom Susceptibility, (3) Thrill and Adventure Seeking, (4) Experience Seeking. Each subscale has two items rated on a scale from 1 (“strongly disagree”) to 5 (“strongly agree”). Results for the general score can range from 8 to 40, with higher scores indicating a higher sensation-seeking trait. Each subscale scores from 2 to 10, with a higher score indicating a higher sensation-seeking dimension rate.

Impulsivity is measured with the Short UPPS-P Impulsive Behavior Scale (SUPPS-P) (47), a 20-item four-dimensional tool: negative urgency (items 6, 8, 13, 15), lack of perseverance (items 1, 4, 7, 11), lack of premeditation (items 2, 5, 12, 19), sensation seeking (items 9, 14, 16, 18), and positive urgency (items 3, 10, 17, 20). Each item is scored from 1 (“strongly disagree”) to 4 (“strongly agree”). The minimum score on each subscale is 4, and the maximum is 16.

Participants’ coping with stress disposition is assessed with the Mini-COPE Stress Management Inventory, which consists of 28 statements divided into 14 strategies (2 statements in each strategy). In addition, strategies can be divided into three subscales: (1) problem-focused strategy, (2) emotion-focused strategy, and (3) avoidance strategy. Participants can answer on a 4-point scale from 1 (“I hardly ever do this”) to 3 (“I almost always do this”).

Emotion dysregulation is measured with a brief version of the Difficulties in Emotion Regulation Scale (DERS) (48). The tool consists of 18 items with six subscales: (1) Non-acceptance of emotional responses (items 7, 13, 14), (2) Difficulty engaging in goal-directed behavior (items 8, 12, 15), (3) Impulse control difficulties (items 9, 16, 18), (4) Lack of emotional awareness (items 1, 4, 6), (5) Limited access to emotion regulation strategies (items 10, 11, 17), and (6) Lack of emotional clarity (items 2, 3, 5). The scale has a five-point Likert scale from 1 (“Almost never”) to 5 (“Almost always”). Total scores range from 18 to 90 and 3 to 15 for each subscale. The higher result means more significant difficulties in emotion regulation.

